
### Child’s psychosocial well-being and functioning (PSYCHLOPS)-Kids

Child’s insight into his/her problems and well-being will be measured using the self-administered PSYCHLOPS-Kids.^36^ The outcome measure assesses three domains, including problems, functioning and well-being. PSYCHLOPS KIDS has three questionnaires forms, that is, pretherapy, during therapy and post therapy version. The tool is designed to be user friendly and can be used for children as young as 7 years. The tool has been feasibility tested as part of pilot study.

### Randomisation and blinding

The unit of randomisation is schools, which will be stratified by gender. Forty middle and high schools nominated by district education authority have been enrolled in the cRCT. Schools will be randomised on 1:1 allocation ratio by independent researcher using computerised software. The 40 schools will be randomised into intervention (n=20) and control arm (n=20). A total of 550 adolescents with psychosocial distress will be recruited from all randomised schools (10–14 adolescents from each cluster). Allocation concealment will be ensured by keeping the random assignments in sequentially numbered sealed envelopes. Due to the nature of the intervention, it is not possible to blind parents, adolescents, school counsellors, intervention supervisors, data and trial manager to the treatment allocation status of trial participants. The AT and principal investigators (PIs) will be blind to the allocation status of school clusters, while the qualitative research team will be un-blind to allocation status of school clusters. To maintain blinding during the trial, intervention and AT will not have any interaction during the trial by being based at separate office locations. The AT will also be non-residents of study subdistrict, Gujar Khan. Furthermore, participants including parents, school administration, head teachers and adolescents will each be individually instructed not to disclose to the AT which type of training they are receiving prior to the commencement of any assessment. Fidelity of blinding will be measured by having assessors guess the condition of each participant at the end of each assessment. We hypothesise that assessors will only be able to correctly guess the condition of participants at a chance rate of nearly 50% at follow-up assessments, indicating that blinding is maintained. The trial statistician will also be blind to the allocation status when developing the statistical analysis plan and writing the statistical programmes. The statistical analysis plan will be validated using dummy randomisation codes. The allocation status of research participants will only be disclosed in a trial steering committee (TSC) meeting after locking of the database on the completion of the trial. In the event of un-blinding, the point of unblinding will be recorded, the assessment will be halted and another assessor will be assigned to complete assessments for that cluster.

### Safety measures

Throughout the study, participants will have access to mental health experts at the IoP. When necessary, they will be referred to a mental health specialist for further assessment for any identified child protection issues or management of severe psychiatric problems including suicidal behaviour. School staff and students in the public-sector schools are entitled to healthcare in public dispensaries and hospitals through an existing referral system. Individuals are able to seek specialist services as walk-in patients and through referrals from primary and secondary healthcare centres. Travel time from the study area to the specialist mental healthcare facility is about 1 hour using public transport. Free of cost ambulance services will be made available in case of a need for referral from PHC centres to the specialist facility. At the specialist facility waiting times are minimal (1 hour at the most) and services are available free of cost. Adolescents at-risk of social protection issues are provided appropriate care through collaboration between the district education department and department of social welfare. We will have additional safeguards that will strengthen these mechanisms and we will initiate the appropriate referral to these local authorities via the IoP should the need arise for health and protection concerns in participants.

The face-to-face contact with the trained school counsellor will ensure that psychological distress is monitored each week, and a measure of distress conducted preintervention and postintervention will be used to supplement this. School counsellors will be well trained to monitor for sudden changes in mood and potential suicidality, including training in how to respond to suicidality with the individual. All staff will be trained in following appropriate referral procedures, via the supervisor and trial coordinator, should a concern for suicide or child protection concern arise.

### Adverse events reporting

A critical incident register will be maintained during the study to record serious adverse events and other adverse events. Recognition and management of all serious adverse events and other adverse events will be included in the training of school counsellors and the research staff. This will include a series of steps which have to be followed once such an event occurs including their detection, classification, reporting requirements and mitigation. Adverse events will be reported to trial ethics committees.

### Data management

All quantitative research data including baseline and follow-up outcome assessment from the research participants will be collected by trained assessors electronically using tablet computers on an android based application named Open Data Kit (ODK). All research data will be remotely uploaded as a Comma Separated Values (CSV) file on the main data server running online using ODK by AT on each day of assessment. The data server will be Good Clinical Practices (GCP) compliant including a date and time stamp for original data entry; an audit trail documenting any subsequent changes will be maintained. Data will be exported from the web server at the end of each day and will be checked for consistency and quality by the data manager. Exported data sets will be stored in password protected computer, only accessible by the data manager. Database will be backed up on a daily basis and the back-up data will be stored on secure hard drives that will be stored in a secure location. Process monitoring data such as supervision attendance, number of supervision meetings conducted and data of number of intervention strategies implemented will be collected in paper form, and this will be manually entered and stored as CSV files. All quantitative research data will be deidentified.

The qualitative data will be collected in audio and paper formats and will be stored in locked filling cabinets. It will be manually entered for analysis by separating the identifying information such as participants’ names and school name from the main data. Identifiable data will never be stored on portable devices unless those devices are stored in secure physical storage. Appropriate firewalls, encryption and password protection will be used for network-connected devices used to store study data. Qualitative data will be recorded on digital recorders with the informed consent of participants, and at the end of each day audio files will be transferred to computers and deleted from portable devices, and stored in a password-protected folders on computers that are backed up daily. The audio files will be destroyed after transcription.

### Statistical analysis

The findings of the trial will be reported following the updated recommendations of the Consolidated Standards of Reporting Trials (CONSORT) 2010 statement: extension to cluster randomised trials.^37^ This will include the flow of clusters and research participants through each stage of the trial, including the number eligible, randomly assigned, receiving the intended treatment, completing the study protocol and analysed for the primary outcome. Initial analyses will compare baseline characteristics of research participants across the two study arms; participants who complete follow-up assessments and participants who could not complete follow-up assessments; and a comparison of the distribution of potential confounding factors. The outcome measures will be summarised at baseline and 3-month post-intervention follow-up by intervention arm and overall. These will be summarised by means (SD), medians (IQR) or numbers and proportions as appropriate (and including age, gender, baseline outcome score), adjusting for cluster. Data will be cleaned and checked for accuracy prior to analysis. The CONSORT flow for the trial is given below (figure 1).

**Figure 1 F1:**
[figure not shown]
Flow of participants through cRCT

For the analysis of the primary outcome (reduction in PSC psychosocial distress scores from baseline to 3 months’ post intervention follow-up), a linear mixed model will be employed with treatment, visit, interaction between treatment and visit as fixed effects, gender and the baseline value of the PSC psychosocial distress score as covariates, subject and cluster (school cluster) as random effects. In addition, adjusted linear mixed model analysis will be performed with the pre-specified covariates (parent/primary caregivers’ education) measured at baseline being added into the above linear mixed model, which will be identified and listed in the statistical analysis plan. The crude and adjusted mean differences in the primary outcome together with its 95% CIs between intervention and control at 3 months will be derived from the mixed models. In addition, subgroup analysis of primary endpoint will be performed on the above pre-specified covariates. Analysis of secondary continuous outcomes with single follow-up measurement will be done using a linear mixed model with treatment as fixed effect, gender and the baseline value of the outcome variable as covariates and cluster (school cluster) as random effect. Analysis of secondary continuous outcomes with repeated follow-up measurement will be performed in a similar fashion as the primary endpoint analysis. The analysis of binary outcomes will use a generalised linear mixed model with treatment as fixed effect, baseline measurement of the outcome variable and gender as covariates, subject and cluster (school cluster) as random effects. The generalised linear mixed model will have a binomial distribution and logit link function, which will generate ORs with their 95% CIs of having an event between intervention and control.

Primary data analyses will be based on the intention-to-treat principle. The per-protocol analyses will also be performed as supplemental analysis. Descriptive statistics will be produced for outcome variables and also for baseline characteristics of participants by treatment arm and visit. Continuous variables will be summarised using number of observations, mean, median, SD, min and max by treatment arm and visit; categorical variables will be summarised by the number and percentage of research participants with mental health problems by treatment arm and visit. Adjusted analysis and subgroup analysis will be based on covariates at baseline without non-missing values.^38^ Detailed imputation methods will be described in the statistical analysis plan. All analyses will be detailed in the statistical analysis plan which will be finalised before the unblinding of the study. No interim analysis of outcomes is planned.

We will conduct a cost-effectiveness analysis to evaluate the cost-effectiveness of EASE intervention in improving outcomes. We will calculate service use for each participant using the data from CSRI.^35^ Service utilisation and the out-of-pocket expenditures of the participants (costs for seeing a doctor or other healthcare provider, admission to hospital, medicines, tests and extra help at home) will be collected at baseline and 3 months postintervention. The data collected through the CSRI will be used to calculate service costs and total costs of care for each participant. Unit costs of services itemised in the CSRI—such as cost per outpatient visit—will be based on locally conducted health facility costing exercises.

Service cost data will subsequently be linked to primary and secondary study outcomes, in particular internalising symptoms scores to assess issues around the value or cost-effectiveness of the EASE intervention. In the event that dominance is not shown, that is, the EASE intervention is more effective but the costs are also more than in the wait-list group, incremental cost-effectiveness ratios will be computed, together with their CIs (using bootstrapping techniques to overcome the expected skewness of the cost data). Results will be plotted on a cost-effectiveness plane and presented as cost-effectiveness acceptability curves to show the probability of the intervention being cost-effective at a range of willingness-to-pay threshold levels. A sensitivity analysis will be conducted to take account of uncertainty and imprecision in the measurements, including multiple imputation models for missing values.

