### Eligibility criteria of participants

#### Inclusion criteria

Adolescents aged 13–15 years.Living with parents/primary caregivers, attending public middle and high schools in the Gujar Khan sub-district of Rawalpindi, Pakistan.Written parent/primary caregiver informed consent or witnessed consent and adolescent assent for participation in the study.Screened positive on self-reported PSC (cut- off score ≥28).Where there is more than one eligible child in a family unit, we will include the youngest eligible child.

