### Sample size calculations

The cluster unit of randomisation has been defined at the school level, stratified by gender. Based on other school-based and community-based mental health interventions using the measures assessing psychosocial problems in children,^15 16^ we assume an effect size of 0.4 at 3 months’ postintervention follow-up, with 80% power, 0.05 significance, an ICC of 0.05 and a two-sided hypothesis test with 40 school clusters randomised with a 1:1 allocation ratio, stratified by gender and accounting for 20% attrition. This results in a total of 550 adolescents (ie, 225 in each arm) and about 14 adolescents from each school. Each high school has about 150 adolescents in grade 8 and 9, which is more than sufficient to meet our sample size requirement. Stratification by gender will minimise imbalance between groups by factors likely to be associated with our outcome and reduce the between-cluster variability, hence increasing the power of the study.

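### The primary model adjusts for the baseline PSC only, although Table 1 also schedules a screening PSC; adding it would be a small, free gain in precision, not the repair of an error

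*Protocol article*

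**What the plan says.** Under Inclusion criteria, entry requires "Screened positive on self-reported PSC (cut- off score ≥28" or more. Recruitment procedure confirms that the assessment team gave the self-rated PSC at screening. The PSC row of Table 1 (Schedule of assessments) is marked in four separate columns: screening, baseline, 1 week and 3 months.

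Under Statistical analysis, in the paragraph after Figure 1, the primary model has treatment, visit and their interaction as fixed effects, with "gender and the baseline value of the PSC psychosocial distress score as covariates, subject and cluster (school cluster) as random effects". The adjusted version adds caregiver education. No section uses the screening PSC for anything except eligibility.

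**The concern.** A single self-report total is a noisy reading of a pupil's usual level of distress. The trial plans two readings of the primary outcome before treatment, and the model uses one. A second reading of the same instrument can explain more of the 3-month score. It can also absorb chance differences between arms in screening severity that the baseline score does not capture, which are possible with 20 schools per arm. The treatment effect stays on the same scale and no data need be added. Only precision is at stake: the width of the confidence interval for the PSC difference at 3 months.

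**Working it through.** **The plan's own figure.** Sample size calculations states "we assume an effect size of 0.4 at 3 months’ postintervention follow-up, with 80% power, 0.05 significance, an ICC of 0.05", "40 school clusters randomised with a 1:1 allocation ratio, stratified by gender and accounting for 20% attrition". For two independent groups this needs 2 × ((1.96 + 0.84)/0.4)², about 98.1, rounded up to 99 per arm. With 14 pupils per school the design effect is 1 + 13 × 0.05 = 1.65, giving 162 per arm. Dividing by 0.8 gives 203 per arm, or 406 in total. The stated result is "This results in a total of 550 adolescents (ie, 225 in each arm) and about 14 adolescents from each school"; 550 is not reproduced, and 2 × 225 = 450. The present point does not depend on this, so power is shown below for both 550 and 450.

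**Inputs for the covariate question.**
- From the documents: ICC 0.05; 40 schools; 20% attrition, so 550 × 0.8/40 = 11 analysed per school; 25% prevalence of distress (Introduction), used as the share above the cut-off.
- Assumed: joint normality; screening-baseline correlation *a* from 0.5 to 0.8; baseline-outcome correlation *b* and screening-outcome correlation *s* from 0.4 to 0.7, with *s* ≤ *b*. All are correlations in unselected pupils.

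**Formulas.** Selecting the top 25% truncates a standard normal screening score at 0.674, which leaves it a variance *v* = 0.242. Among enrolled pupils:
- Var(baseline) = 1 − *a*²(1 − *v*)
- Var(outcome) = 1 − *s*²(1 − *v*)
- Cov(baseline, outcome) = *b* − *as*(1 − *v*)
- Residual variance given baseline: R1 = Var(outcome) − Cov²/Var(baseline)
- Residual variance given both (unaffected by truncation on screening): R2 = 1 − (*b*² + *s*² − 2*abs*)/(1 − *a*²)

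**Worked case**, *a* = 0.7, *b* = *s* = 0.6:
- Var(baseline) = 1 − 0.49 × 0.758 = 0.628; Var(outcome) = 1 − 0.36 × 0.758 = 0.727; Cov = 0.6 − 0.42 × 0.758 = 0.281.
- R1 = 0.727 − 0.281²/0.628 = 0.601.
- R2 = 1 − (0.36 + 0.36 − 0.504)/0.51 = 0.576.
- Reduction = 1 − 0.576/0.601, about 4.1%.

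**Other cases:**

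| *a* | *b* | *s* | R1 | R2 | Reduction |
|---|---|---|---|---|---|
| 0.5 | 0.5 | 0.5 | 0.692 | 0.667 | 3.6% |
| 0.7 | 0.7 | 0.7 | 0.457 | 0.424 | 7.3% |
| 0.8 | 0.5 | 0.5 | 0.735 | 0.722 | 1.8% |
| 0.8 | 0.4 | 0.4 | 0.831 | 0.822 | 1.0% |
| 0.5 | 0.7 | 0.7 | 0.395 | 0.347 | 12.3% |
| 0.7 | 0.6 | 0.5 | 0.632 | 0.628 | 0.8% |
| 0.7 | 0.6 | 0.42 | 0.640 | 0.640 | 0 |
| 0.8 | 0.5 | 0.40 | 0.750 | 0.750 | 0 |

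The gain vanishes when *s* = *ab* (0.7 × 0.6 = 0.42; 0.8 × 0.5 = 0.40), because screening then says nothing about the outcome beyond baseline. On a grid in steps of 0.05 over the assumed ranges, the reduction runs from 0 to 12.3%, with median about 1.5%.

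**Effect on the treatment estimate.** The variance of a school mean is proportional to ICC + (1 − ICC)/11. The pupil-level share is (0.95/11)/(0.05 + 0.95/11) = 63%. Multiplying each reduction by 0.63 gives at most 4% in 94% of the grid, and 7.8% at the extreme. That takes the ICC of 0.05 as holding after baseline adjustment. If instead the school variance stays at 5% of the enrolled pupils' outcome variance (0.628) while baseline removes only pupil-level variance, the extreme case has 0.395/0.628 = 0.630 and 0.347/0.628 = 0.552. The reduction is then 1 − (0.05 + 0.95 × 0.552/11)/(0.05 + 0.95 × 0.630/11), about 6.4%. Hence about 7% at the extreme.

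**Effect on power.** This used slightly different assumed correlations (*a* 0.6-0.8; *b* = *s* from 0.3 to 0.6), truncation at entry, and the same proportional reduction applied at both levels.
- 550 enrolled: 92.9% unadjusted, 93.5-97.0% with baseline only, 93.6-97.6% with both.
- 450 enrolled: 90.2-94.9% with baseline only, 90.4-95.8% with both.

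The largest gains are about 0.6 and 0.9 percentage points.

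**The case against.** The strongest reply is that nothing here is wrong. A mixed model adjusted for baseline outcome, gender and school is standard and valid, and baseline PSC already captures most of the prognostic information and most of any chance imbalance in severity. Baseline is also the later reading, so it may well correlate more strongly with follow-up than screening does, and the gain can then fall to nothing. All of that stands, and it limits the point to an optional improvement.

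A reader might go further and infer that selection at 28 or more makes the single-baseline analysis biased through regression to the mean. The documents do not support that. One entry rule applies to all pupils, so the expected fall after selection is common to intervention and wait-list arms and drops out of the between-arm difference that the model estimates.

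A second reply is that two administrations are not certain. The Outcome measures and Primary outcome text lists only baseline, 1 week and 3 months, and no interval between screening and baseline is given. Table 1's separate columns favour two administrations, but the authors need to confirm it.

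A third is that the statistical analysis plan, not shown here, may list further covariates. The article leaves the adjusted model's list to that plan. It does itself state the covariates of the primary model, and that stated choice is what is discussed here.

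**Conclusion.** The point holds as a minor efficiency suggestion. The stated primary model is sound, and no conclusion of the trial is likely to turn on this. If screening and baseline PSC are separate administrations, using both would probably cut the variance of the treatment effect by 0-4%, with about 7% as the extreme. These sizes rest on assumed correlations, joint normality and a 25% share above the cut-off; the restricted range of screening scores among enrolled pupils keeps them small. There is no gain if one form supplied both values, or if screening carries no information beyond baseline.

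**What to change.** Before unblinding, confirm from the data records that the screening and baseline PSC were completed on separate occasions. If so, enter the screening PSC total as a second prespecified covariate beside the baseline PSC in the primary model, and hence in the adjusted model built on it. If one form served as both, state that in the analysis plan and leave the model as it is.

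The cost is one sentence in the plan and one degree of freedom. The screening score should be known for every enrolled pupil, since entry depended on it, so no participant is lost and nothing new is collected. The article says the analysis plan is finalised before unblinding, which leaves room for the change.

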## Methods and analysis

### Study design

A two-arm, single-blind, cRCT, with a wait-list control arm and an embedded qualitative study is being conducted in public schools of rural subdistrict of Gujar Khan in Rawalpindi, Pakistan. The unit of randomisation is a school. In this study, 40 eligible school clusters, stratified by gender, have been randomised into intervention and control arms with a 1:1 allocation ratio. Outcomes will be assessed at baseline and 1 week and 3 months postintervention.

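### The logistic mixed model for binary outcomes has a subject random effect but no visit or treatment-by-visit term, so its odds ratio is either not determined by the data or averaged over two visits

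*Protocol article*

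**What the plan says.** The Statistical analysis section of the protocol article sets out three model forms.

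- **Primary outcome and repeated continuous secondary outcomes.** The fixed effects are "treatment, visit, interaction between treatment and visit as fixed effects", with gender and baseline score as covariates and with subject and school as random effects. For the primary outcome, the mean difference "between intervention and control at 3 months will be derived from the mixed models".
- **Continuous secondary outcomes with one follow-up.** Treatment is the fixed effect, with "gender and the baseline value of the outcome variable as covariates and cluster (school cluster) as random effect". There is no subject effect.
- **Binary outcomes.** The model is a "generalised linear mixed model with treatment as fixed effect, baseline measurement of the outcome variable and gender as covariates, subject and cluster (school cluster"), with subject and school both random, a binomial distribution and a logit link, "which will generate ORs with their 95% CIs of having an event between intervention and control". No visit term appears and no time point is attached to the OR.

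Under Study design, "Outcomes will be assessed at baseline and 1 week and 3 months postintervention". Table 1 shows that most measures are taken at both follow-ups, while two (PaedS and CSRI) have only the 3-month follow-up. The section also says that "categorical variables will be summarised by the number and percentage of research participants with mental health problems by treatment arm and visit", and that "All analyses will be detailed in the statistical analysis plan which will be finalised before the unblinding of the study".

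**The concern.** The two continuous models are paired correctly. Where there are repeated follow-ups, visit terms and a subject effect appear together. Where there is one follow-up, both are absent. The binary model has the subject effect without the visit terms, so it fits neither data structure.

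If one follow-up is analysed, the model asks for a between-subject variance that a single yes/no response per subject can hardly inform. The conditional OR depends on that variance, so the reported figure could depend on starting values, quadrature or software defaults. If both follow-ups are analysed, the model can be fitted, but it returns one treatment effect for two visits. The aim, the primary hypothesis and the primary contrast are all set at 3 months, and this model has no term from which a 3-month OR could be read.

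**Working it through.** The protocol gives no figure for the binary analysis, so there is nothing of its own to reproduce. The check compares the three specifications and then tests the binary one on simulated data.

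**1. Terms side by side**

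| Model | Visit and treatment-by-visit | Subject random | School random |
|---|---|---|---|
| Primary / repeated continuous | yes | yes | yes |
| Single-follow-up continuous | no | no | yes |
| Binary | no | yes | yes |

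The instruction to proceed as for the primary endpoint is attached only to continuous outcomes with repeated follow-up. It does not supply the missing terms to the binary model.

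**2. Simulation inputs**

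From the protocol: 40 schools, about 14 adolescents per school (40 × 14 = 560), 1:1 allocation, and two follow-ups.

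Assumed, because the protocol gives no values for binary outcomes: subject SD 1.5 and school SD 0.4 on the logit scale, visit effect −0.3, gender effect 0.3, and a continuous baseline covariate with coefficient 0.6. Fitting was by marginal likelihood with Gauss–Hermite quadrature:

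logit P(event) = intercept + β·treatment + gender + baseline + subject + school.

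**3. One follow-up per subject**

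One simulated data set was used, with the 3-month response only. The subject SD was fixed at successive values and the likelihood maximised over the remaining parameters.

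| Subject SD | Log-likelihood | Treatment OR |
|---|---|---|
| 0.001 | −359.505 | 0.634 |
| 0.5 | −359.494 | 0.618 |
| 1 | −359.483 | 0.578 |
| 1.5 | −359.477 | 0.528 |
| 2 | −359.473 | 0.476 |
| 3 | −359.469 | 0.376 |
| 4 | −359.480 | 0.291 |

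The log-likelihood ranges over 359.505 − 359.469 = 0.036, which is too flat to prefer any of these values. The OR runs from 0.63 to 0.29 over the same range.

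**4. Both follow-ups**

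Each scenario used 12 replicates, with the same random seeds across scenarios.

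| True OR, 1 week / 3 months | Geometric mean of the two | Model as written | 3-month OR with visit and treatment-by-visit added |
|---|---|---|---|
| 0.41 / 0.67 | exp[(−0.9 − 0.4)/2] = 0.52 | 0.58 | 0.68 |
| 0.67 / 0.41 | exp[(−0.4 − 0.9)/2] = 0.52 | 0.60 | 0.44 |
| 0.55 / 0.55 | exp(−0.6) = 0.55 | 0.62 | 0.58 |

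Opposite time courses give almost the same answer (0.58 and 0.60) under the model as written. With the visit terms the 3-month OR is approximately recovered (0.68 for 0.67; 0.44 for 0.41). The constant-effect row shows how coarse the exercise is: even there the model as written gives 0.62 against a true 0.55. With 12 replicates, the runs show the pattern and do not give precise sizes.

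**The case against.** The strongest reply is that no analysis in the article is visibly affected. Every effectiveness outcome under Primary outcome and Secondary outcomes is a score, no responder definition is given, and the Hypotheses section contains nothing binary. The sentence reads like a general fallback, and full detail is promised in a statistical analysis plan that is not shown. Since the protocol uses a subject effect only for repeated follow-up, naming it here probably signals repeated data, which makes the single-visit reading less natural. An OR averaged over two scheduled visits is also a legitimate secondary quantity, and the binary sentence does not promise a 3-month OR.

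Much of this stands, and it limits the reach of the point. It does not remove it. The article is not silent on the binary model: it lists the fixed effect, covariates, random effects, distribution, link and output, and the listed terms do not belong together. If an average over visits is wanted, the plan should say so, because everything else is aimed at 3 months.

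A reader might infer four stronger things that the documents do not support.

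- **That the single-visit model is strictly unidentifiable.** The shape of the logistic-normal curve carries a trace of information on the subject variance. The accurate statement is that it is not identifiable in practice.
- **That the pooled OR overstates the 3-month effect.** The direction depends on an assumed time course. The effect is overstated when it fades (0.58 against a true 0.67) and understated when it grows (0.60 against a true 0.41).
- **That the subject effect inflates the log OR by a known percentage.** The gap between a subject-conditional OR and one without a subject effect is a difference between two quantities and is not a bias. The repeated-measures form recommended here keeps the subject effect.
- **That baseline PSC caseness would be a near-constant covariate because all participants entered at 28 or above.** The cut-off applies at screening. Table 1 lists a separate baseline PSC, the article does not say that all participants are still above the cut-off then, and it does not propose PSC caseness as an outcome.

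**Conclusion.** The binary model is badly specified as written and should be corrected. With a single follow-up, its subject variance, and therefore its conditional OR, cannot be identified in practice. In the simulated data set, ORs from 0.63 to 0.29 fitted equally well. With both follow-ups, it gives an average over 1 week and 3 months that in general equals the 3-month OR only when the effect is constant, and it can err in either direction.

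The sizes rest on assumed effects and variance components and on small simulations (one data set for the first case, 12 replicates per scenario for the second). The structural conclusion follows from the listed terms and does not depend on those values. The consequence is confined to secondary or supplementary binary analyses, none of which is named. The primary endpoint model contains the right terms and is unaffected. The unseen analysis plan may already put this right.

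**What to change.** State which binary outcomes will be analysed and at which visits, then match the model to the data as the protocol already does for continuous outcomes.

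- **Binary outcomes measured at both follow-ups:** treatment, visit and treatment-by-visit as fixed effects; baseline and gender as covariates; subject and school as random effects; report the 3-month OR with its 95% CI.
- **Binary outcomes with one follow-up:** treatment as fixed effect; baseline and gender as covariates; school as the only random effect.

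The cost is a few lines in the statistical analysis plan and a note of the change from the published protocol, made before unblinding. No additional data or participants are needed, and the primary analysis does not change.
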